
**Figure 1 Fig1:**
[figure not shown]
***Shamba Maisha***
**causal framework**

Drawing upon this framework, we developed the intervention framework to describe the pathway by which we believe the multisectoral agrigultural intervention impacts on mediating factors and eventually improves health outcomes among HIV-infected adults (Figure 2). Specifically, we hypothesized that: 1) The three intervention components together would directly lead to improvements in food security and household wealth (most proximal mediators); 2) Changes in food security and household wealth would, in turn, contribute to less macronutrient and micronutrient malnutrition (nutritional pathway), less anxiety, stress and depression (mental health pathway), improved ART adherence and retention in care (behavioral pathway) and improved gender empowerment; and 3) Through these pathways, the intervention would ultimately contribute to decreased HIV morbidity and mortality and fewer HIV transmission risk behaviors.

**Figure 2 Fig2:**
[figure not shown]
***Shamba Maisha***
**intervention framework**

### Randomization

We used a two-step process to select two sites from among 68 government health facilities in Rongo, Migori and Nyatike districts supported by Family AIDS Care & Education Services (FACES), a collaboration between the University of California, San Francisco (UCSF), and the Kenyan Medical Research Institute (KEMRI) (Lewis Kulzer et al. 2012). First, we limited to 20 sites where there were an adequate number of PLHIV on ART at the time of the study, and where farming was a primary means of livelihood in the communities. Next, we selected two government health facilities for the pilot randomized controlled trial (RCT) according to the following criteria: a) having adequate numbers of PLHIV on ART with non-overlapping catchment areas; b) having catchment areas that were relatively similar to one another according to rainfall patterns, health, topography and socioeconomic status; and c) meeting practical requirements for the intervention, including acceptable characteristics in topography to enable use of the water pump, having water access year round, and having favorable soil composition to potentiate the intervention. One site was randomly selected as the intervention site and the other the control site by the study’s biostatistician who used a computer random number generator and was not involved in fieldwork. Clinics, healthcare providers, patients, and researchers involved in implementing the study were not blinded to the allocation.

### Ethics statement

The study was approved by the Committee on Human Research at UCSF and the Ethical Review Committee at KEMRI. All participants in the study gave written informed consent prior to enrollment in the study, and had the cost of their transportation reimbursed up to 800 Ksh per clinic-based interviews (~$9.4 USD) and 400 Ksh for home-based interviews (~$4.70). This clinical trial was registered at ClinicalTrials.gov (NCT01548599).

### Participants and recruitment

The study population includes HIV-infected patients between the ages of 18–49 years receiving ART, have access to farm land and surface water, and have demonstrated evidence of moderate to severe food insecurity or malnutrition during the year preceding the study. Participants were recruited from Rongo (intervention site) and Migori (control site) District Hospitals in Nyanza Province beginning in April 2012. Research assistants introduced the study to patients waiting to be seen at the HIV clinic at the two health facilities. Individuals who expressed interest were consented and screened for eligibility. Among interested and potentially eligible individuals, home visits were conducted to verify that the participant had access to farming land and surface water. In addition to the eligibility criteria above, the study also aimed to ensure that at least 40% of participants at each site were of each gender. Individuals who met eligibility criteria were enrolled in the study after providing written informed consent. At intervention sites, participants were enrolled in a savings program in anticipation of receiving the asset loan. Control participants also agreed to save the down payment (~$6) required for the loan by the study end. A total of 140 HIV-positive individuals were enrolled in the study during the period of April – July 2011 (See Figure 3); an additional two (1.4%) eligible screened participants declined to participate in the study.

**Figure 3 Fig3:**
[figure not shown]
***Shamba Maisha***
**consort diagram**

### Data collection

Participants were followed quarterly for structured interviews and ART adherence assessments by unannounced pill counts at their home. Anthropometry (i.e., mid upper arm circumference measurements [MUAC] and BMI measurements) and phlebotomy for viral load and CD4 determinations were conducted every six months. Viral load testing was performed on venous blood at the Centers for Disease Control-Kenya laboratory on the COBAS TaqMan HIV viral load platform (Roche Molecular Diagnostics, Pleasanton, CA) with a lower limit of detection of <20 copies/mL. Absolute CD4 count testing was performed on whole blood using the BD FACSCount (BD Bioscience, San Jose, CA). In addition, clinical data were abstracted from participant’s medical records.

Structured interviews for clinical and sensitive behavioral data were administered at baseline, 6 months and 12 months at the clinic and included the following data (see Table 1): health care access and competing demands, ARV history and adherence, physical and mental health, social support, women’s empowerment, stigma, HIV disclosure, alcohol use, and sexual behavior. Additionally, quarterly home visits were conducted to collect unannounced pill counts for ART adherence, food frequency, food security, income, housing, assets and wealth, and specific data related to agricultural output, labor, harvesting, marketing, and irrigation.

**Table 1 Tab1:** **Measurements**

**Path**	**Measurement**	**Definition**	**Frequency**
**Nutritional Pathway**	Nutritional status	Nutritional status was assessed through body mass index (BMI) and mid-upper arm circumference (MUAC), commonly used to assess nutritional status (Physical Status 1995; Collins et al. 2000). The BMI reflects protein and fat reserves (James et al. 1988) and was assessed using an established grading system (Ferro-Luzzi et al. 1992). For MUAC, we used WHO sex-specific cut-offs of 22.0 cm for females and 23.0 cm for males with chronic energy deficiency (Doocy et al. 2005).	Semi-annually
	Food frequency	Food frequency, the number of different foods or food groups and the frequency consumed over a given reference period (Hoddinott & Yohannes 2002), as adapted from the World Food Programme Food Consumption Score was collected.	Quarterly
**Behavioral Pathway**	Pill count ART adherence	Participants received an unannounced visit to inventory medications and count pills (Bangsberg et al. 2001a; Bangsberg et al. 2001b; Bangsberg et al. 2000), a technique closely correlated with electronically monitored adherence, HIV viral load (Bangsberg et al. 2000) and progression to AIDS (Bangsberg et al. 2001c). The count of existing pills was reconciled with the participant’s pharmacy refill history to determine the percentage of pills not yet consumed.	Quarterly
	Competing demands	Questions were modified from Gelberg and Anderson’s Behavioral Model for Vulnerable Populations (Gelberg et al. 2000; Gelberg et al. 1997) to assess how often lack of food interferes with ability to procure drugs or visit the clinic.	Semi-annually
	Healthcare access	Utilization of health care services including hospitalizations and clinic visits over the preceding 6 months were collected.	Semi-annually
**Mental Health Pathway**	Mental health & depression	Mental health status was measured using the Medical Outcomes Study HIV Health Survey (MOS-HIV), a tool for assessing health-related quality of life (Wu et al. 1991) that has been validated in resource-limited settings (Chatterton et al. 1999; Mast et al. 2004). Depression was screened using the Hopkins Symptom Check-list for depression, a 15-item scale (Derogatis et al. 1974) which has been validated in sub-Saharan Africa (Bolton et al. 2004).	Semi-annually
	HIV-related stigma	We used the Internalized AIDS-Related Stigma Scale (Kalichman et al. 2009).	Semi-annually
	Disclosure of HIV status	We asked about disclosure of HIV status to partners, family members, friends, colleagues, and public. These questions were adapted from our previous studies in Uganda, Botswana and Swaziland (Weiser et al. 2007; Wolfe et al. 2008; Tsai et al. 2013).	Semi-annually
	Alcohol use	To measure alcohol use, we adapted the Alcohol Use Disorders Identification Test (AUDIT-C) indicators. The AUDIT-C is a 3-item alcohol screen that can help identify persons who are hazardous drinkers or have active alcohol use disorders.	Semi-annually
**Empowerment**	Gender empowerment	Empowerment indicators were adapted from a large cluster-randomized trial of an intervention including: greater challenges to established gender roles, communication with relationship partner about sexual matters in the prior 3 months, measures of financial decision-making, measures of attitudes towards gender roles and gender-based violence, and experience of controlling behavior by relationship partner in prior 3 months (Pronyk et al. 2006). In addition, we used the Sexual Relationship Power Scale (SRPS) (Pulerwitz et al. 2000), which conceptualizes sexual relationship power as a multi-dimensional construct consisting of relationship control and decision making dominance. The SRPS has been used successfully in observational research conducted in South Africa (Dunkle et al. 2004; Jewkes et al. 2010) and Uganda.(Weiser et al. 2010a, b) We also collected data on sexual victimization and perpetration in the prior 3 months.	Semi-annually
**Proximal Mediators**	Food insecurity	The Household Food Insecurity Access Scale (HFIAS) has been validated in eight countries (Coates et al. 2006a; Swindale & Bilinsky 2006; Frongillo & Nanama 2006; Coates et al. 2006b) and used successfully by our team in rural Uganda. (Weiser et al. 2010a; Tsai et al. 2011; Weiser et al. 2012; Tsai et al. 2012; Weiser et al. 2010a, b; Miller et al. 2011; Tsai et al. 2011)	Semi-annually
	Agricultural measures	Agricultural measures were adapted from outcome evaluations developed by Kickstart in Kenya and supplemented by outcome indicators found in an earlier pilot study and a rural assessment. These measures were designed to evaluate uptake and adoption, and to measure changes in agricultural practices including crop diversity and agricultural practices and production. In addition, we evaluated the effectiveness of the training, and specific topics within, so as to refine the training for the subsequent larger cluster-randomized trial.	Quarterly
	Household economic indicators	A modification of the World Bank Living Standards Measurement Study (LSMS) questionnaire (Grosh & Glewwe 1998) was used to measure: a) expenditures (food, health, education and productive investments); b) consumption (food and non-food); c) income (from agriculture and all sources); and d) inter-household commodity and cash transfers.	Quarterly
**Behavioral Outcome**	Risky sexual behaviors	The primary transmission risk outcome was unprotected sex. Other outcomes included: number of non-spousal/non-cohabiting sexual partners, sex-exchange (exchanging sex for money, food, or other resources) Dupas & Robinson 2010); Robinson & Yeh 2011).	Semi-annually
**Health Outcomes**	HIV-related mortality	Burial permits and information from family members were used to determine cause of death.	As needed
	Viral load suppression	Viral load testing was performed on venous blood on the COBAS TaqMan HIV viral load platform (Roche Molecular Diagnostics, Pleasanton, CA) with a lower limit of detection of <20 copies/mL.	Semi-annually
	CD4 Count	We abstracted data for CD4 counts from participant’s medical records. Absolute CD4 count testing was performed on whole blood using the BD FACSCount (BD Bioscience, San Jose, CA).	Semi-annually
	HIV morbidity	HIV morbidity was measured through key outcomes from the medical record. We abstracted data every 3 months for ART treatment interruptions and episodes of opportunistic infections. We also gathered self-report data on opportunistic infections and symptoms during structured interviews.	Quarterly/Semi-annually
	Physical health	Health status was measured using the MOS-HIV, a tool for assessing health-related quality of life (Wu et al. 1991) that has been validated in resource-limited settings (Chatterton et al. 1999; Mast et al. 2004).	Semi-annually
**Covariates**	Demographics	Age, religion, education, marital/partnership status, number of children and household census.	Baseline
	Social support	To measure social support, we adapted the Functional Social Support Scale (Antelman et al. 2001), a modified version of the Duke University-University of North Carolina Functional Support Questionnaire (Broadhead et al. 1988) consisting of questions related to perceived emotional and instrumental support. Higher scores reflect higher levels of social support.	Semi-annually
	ART history and Self-reported ART adherence	Detailed ART history, ART self-reported adherence and barriers to ART adherence were collected. For self-report adherence, we used the visual analog scale (Oyugi et al. 2004) and the three day recall.	Semi-annually

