### Description of intervention

The *Shamba Maisha* intervention consisted of three components: 1) a microfinance loan (~$150) to purchase the farming commodities, 2) a micro-irrigation pump, seeds, fertilizer and pesticides, and 3) trainings in sustainable agricultural practices and financial literacy. KickStart, an international non-governmental organization (NGO), along with technical support of agricultural experts from the University of California Davis, led the agricultural component of the intervention. *Adok Timo*, a microfinance institution in Nyanza Province, implemented the economic aspects of the intervention with support from the UCSF and KEMRI research team. The intervention components are described below.

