#### Loan program

The microfinance loans were managed by *Adok Timo,* which has branches in Nyanza Province. The intervention group received training on financial management and marketing skills prior to receiving the loan. All trainings took place on participant’s farms or a nearby location. Participants were required to save 500 Kenyan shillings (~$6.00 USD) prior to receiving the loan. Each participant received vouchers to purchase the following items: the Hip Pump, 50 feet of hosing, fertilizer, and government certified seeds. These materials were purchased at a local farm store (“agrovet”). Loan repayment could begin at any time, but farmers were expected to make a minimum payment after the first harvest, usually 4–6 months after planting. Farmers were expected to repay in full by the end of two harvest seasons (approximately one year); however, if regular payments have been made, this deadline was extended based on the guidelines set out by the microfinance institution. Participants were not asked to forfeit personal belongings to cover loan payments. Control participants were eligible for the microcredit loan and the *Kickstart* Hip Pump at the end of the 1-year follow-up period.

KickStart water pump and agricultural training: Irrigation technologies have been shown to improve agricultural output. (About KickStart) Recognizing the need for improved agricultural tools for poor farmers in Kenya, Kickstart developed a low-cost irrigation pump. These pumps enable farmers to irrigate their crops year-round avoiding dependence on seasonal rainfall thus capitalizing on higher crop prices in the marketplace. In prior evaluations in Kisumu Kenya, farmers using this hip pump have been able to enjoy up to a ten-fold increase in income (Brandsma 2003; Kihia & Kamau 1999; Stevens 2002; World Bank 2010).

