#### Analysis of outcome data

This pilot was not powered for formal significance testing of the intervention effect on primary health, behavioral and gender empowerment outcomes. Rather, analyses will focus on assessing the effects of the intervention on proximal mediating factors (Figure 2), and separately on primary outcomes. Analyses for mediating variables will generally treat scores as continuous measures. For example, food security will be measured using the Household Food Insecurity Access Scale (HFAIS) score at the 1-year visit; change in household economic indicators over the 1-year follow-up period will be measured by subtracting baseline from 1-year follow-up data for household expenditures, consumption and income (from agricultural and other sources). Initial comparisons will be based on group-specific descriptive summaries of observed outcomes and rank-based tests comparing outcomes between groups. We will also use regression methods to compare outcomes between groups and control for baseline characteristics. Analyses for primary health outcomes will proceed similarly, with appropriate choices of model for outcome type. For example, we will use pooled logistic regression for between-group comparisons of rates of viral load suppression, and mixed effects regression to compare changes in CD4 counts between groups. We will also make preliminary assessments of degree of mediation in models for primary outcomes via inclusion of mediating factors, with assessment of direct and indirect intervention effects of key mediating variables (Petersen et al. 2006). Finally, we will also perform intent-to-treat and per-protocol analyses of the pilot data, with the per-protocol subset limited to participants that obtained and used the intervention consistently over the 12-months of follow-up. Although these analyses will likely be underpowered for formal testing purposes, the resulting estimates and confidence intervals will be important for planning for the subsequent RCT.

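### Household expenditure counts productive investments, which the intervention finances in one arm only, so its change may partly record delivery of the intervention

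*Protocol article*

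**What the plan says.** In the protocol article, Table 1 (Proximal Mediators, Household economic indicators) lists four measures from a modified living-standards questionnaire, collected quarterly. The first is "expenditures (food, health, education and productive investments"). Consumption, income and transfers between households are listed beside it as separate measures.

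Analysis of outcome data says that change in the economic indicators will be "measured by subtracting baseline from 1-year follow-up data for household expenditures, consumption and income". The same section plans "preliminary assessments of degree of mediation in models for primary outcomes via inclusion of mediating factors". The causal framework names "improvements in food security and household wealth (most proximal mediators") as the first step through which the intervention is meant to act.

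Description of intervention includes "a microfinance loan (~$150) to purchase the farming commodities". Loan program adds: "Each participant received vouchers to purchase the following items: the Hip Pump, 50 feet of hosing, fertilizer, and government certified seeds". Control participants become eligible for the loan and pump only when the one-year follow-up ends.

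**The concern.** A pump, hosing, fertilizer and seed bought for farming are productive investments in the ordinary sense of the term. The treatment puts these items into one arm during follow-up and withholds them from the other. An indicator that counts such spending can therefore rise in the intervention arm because the intervention was delivered, whether or not any household is better off. Input purchases paid for by a loan are a cost of production and are not evidence of wealth.

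Two uses would be affected. The between-arm contrast in expenditure could be read as an early sign of improved household wealth. If expenditure also enters the mediation models, a variable that partly marks receipt of treatment would distort the split between direct and indirect effects. The pilot makes no powered claim, but the article says that its estimates and intervals will be used to plan the larger trial, so a bias here could carry forward.

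**Working it through.** The article gives no sample size, power or effect size for this indicator, so there is no figure to reproduce. The check has two parts: whether the definition overlaps with the treatment, and how large the direct contribution could be.

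**Overlap**
- Measure: expenditure includes productive investments (Table 1).
- Treatment: the loan and vouchers pay for farm equipment and inputs (Description of intervention; Loan program).
- Timing by arm: intervention during follow-up, control only afterwards (Loan program).
- The text shown has no rule that excludes or separates study-financed purchases.

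The overlap therefore follows from definitions that the article states.

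**Inputs for size**
- Loan: about $150.
- Baseline monthly household income (Table 2): intervention $104 (SE 21.3, n = 72); control $273 (SE 53.1, n = 68).
- Recall period: not stated. Assumed to be 1, 3, 6 or 12 months.
- SD of change in expenditure: not given. The SD of baseline income is used as a stand-in, which is an assumption.

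**SDs recovered as SE × √n**
- Intervention: 21.3 × √72 = $181.
- Control: 53.1 × √68 = $438.
- Pooled: √[(71 × 181² + 67 × 438²)/138] ≈ $332.

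**Direct addition if the whole purchase falls inside the recall window of the one-year interview and is coded as household spending** (150 ÷ months of recall)

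| Assumed recall | Added per month | Share of $104 | In SD units (SD $181 to $332) |
|---|---|---|---|
| 12 months | $12.5 | 12% | 0.07 to 0.04 |
| 6 months | $25 | 24% | 0.14 to 0.08 |
| 3 months | $50 | 48% | 0.28 to 0.15 |
| 1 month | $150 | 144% | 0.83 to 0.45 |

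If the purchase precedes the window, or if voucher items are not coded as household spending, the addition is $0.

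**Chance that the purchase alone gives p < 0.05**, two-sided normal approximation at person level, with SE = SD × √(1/72 + 1/68) = SD × 0.169:
- 12 months: 0.07 to 0.06.
- 6 months: 0.13 to 0.07.
- 3 months: 0.37 to 0.14.
- 1 month: 1.00 to 0.76.

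These probabilities only indicate scale. They ignore the one-clinic-per-arm design, and the pilot plans no formal powered test.

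**Which row is plausible.** The purchase comes after the training and the required saving, and before the first planting. A first minimum payment is expected after the first harvest, usually 4–6 months after planting, and two harvest seasons take about a year. The purchase thus probably falls early in follow-up. With a recall of three months or less it would then lie outside the one-year window and add nothing. With 12-month recall it could be captured at about $12.5 a month. The larger figures need a late purchase inside a short window, and nothing in the article points to that.

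**The case against.** The strongest objection is that the planned measure is the one-year value minus baseline, not spending accumulated over the year. A reader might infer that the loan-financed items must raise measured expenditure. The article does not support that: with an early purchase and a short recall period the direct addition is zero, and voucher items may not be coded as household spending at all. Such coding normally sits in the questionnaire or the analysis plan, so its absence from an article is not a fault. This stands, and it limits the point to a possible bias.

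A reader might also infer that loan repayments would count a second time. Repayments are not among the listed expenditure categories, so there is no basis for that.

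It is also fair to say that the article does not state that the four categories are summed, does not make gross expenditure the lead indicator, and does not say which economic measure will enter the mediation models. Consumption and income are measured separately, and the purchase does not directly inflate either. Later spending on seed or fertilizer from a household's own money would be a real response to the intervention, though still not wealth in itself.

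The stated definition remains. Productive investments are placed inside a measure that will be compared between arms as an economic mediator, while the treatment finances productive investments in one arm.

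**Conclusion.** The point holds as a conditional one. As defined, the change in household expenditure may partly record delivery of the intervention rather than improved household wealth. The direct addition runs from $0, if the purchase precedes the one-year recall window, to about $12.5 a month (12% of intervention-site baseline income) with 12-month recall. It exceeds that only if the purchase falls inside a shorter window.

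These figures assume that the full loan is spent on the listed items and that voucher purchases are coded as household expenditure. The SD-based figures also rest on income as a stand-in for change in expenditure. Any direct bias would run upwards in the intervention arm, and the consequence is for planning estimates, since the pilot makes no confirmatory claim. The remedy is right whatever the recall period turns out to be.

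**What to change.** For the between-arm comparison and any mediation model, define the expenditure measure as food, health and education, without productive investments. If productive investments must stay in, leave out at least the inputs financed by the study loan or vouchers. Report productive investments as a separate line, so that a real change in farm investment is still visible. Use the separately measured consumption when interpreting results as household welfare. State the recall period and the coding of voucher purchases beside the result.

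The cost is a derivation rule and possibly a less favourable expenditure figure. No new data are needed if the categories are recorded as Table 1 lists them. Leaving out the whole category is the simpler option, because it does not require identifying which individual purchases the study paid for.
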